### 2.7. Statistical analysis

All statistical analyses will be conducted using SPSS statistical software (version 24.0, SPSS, Inc., Chicago, IL, USA). The study will undertake a comparative analysis of two intervention sequences and investigate the existence of carry-over effects. This will involve conducting *t*-tests on the change of each sequence for all crossover endpoints (Wellek and Blettner, 2012; Jones and Kenward, 2014). For variables that do not show significant carry-over effects, we will compare the changes during specific interventions in both sequences. For variables that show significant carry-over effects, we will compare the changes in specific interventions during the first period. To confirm the normal distribution of the data, we will analyze the skewness and kurtosis and perform the Shapiro-Wilk and Kolmogorov–Smirnov tests. Firstly, the differences between rhythmic sequences will be compared using repeated measures ANOVA (RMANOVA) and the Bonferroni correction for pairwise comparisons. If the data do not satisfy a normal distribution, Friedman’s test one-way analysis of variance (ANOVA) will be performed. Secondly, Pearson’s correlation test will be used to calculate the correlations between RAT performance and behavioral outcome measures. Thirdly, differences of EEG band activities between the types of rhythmic sequences and the tasks will be compared using RMANOVA with Bonferroni correction. Lastly, comparisons between interventions will be performed using a two-tailed *t*-test or Mann–Whitney U test depending on normality.

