## 2. Methods

### 2.1. Study design

Randomized crossover trials, clinical experiments in which participants are assigned randomly to a sequence of treatments and each participant serves as one’s own control in estimating treatment effect (Senn, 2002; Piantadosi, 2005), will be used in the present study. Participants will be assigned randomly to either rhythm training followed by cognitive training or cognitive training followed by rhythm training (Figure 1). For both groups, pre- and post-training evaluations will be administered immediately before training and after the 4th week of training. Participants will have a 4-week washout phase between trainings to minimize a possible carryover effect (Senn, 2002; Piantadosi, 2005). Pre- and post-training evaluations will include diagnosis questionnaires, cognitive evaluation tools, and resting EEG measurement.

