### 2.3. Recruitment

Participants who have met the eligibility criteria will be enrolled in the study after they provide informed consent. Participants and their parents will receive oral and written information detailing the purpose of the study. All experimental protocols will be approved by the Institutional Review Board of Hanyang University Medical Center. Approximately 40 children with ADHD will be recruited through Hanyang Medical Center outpatient clinics or online recruitment posts. The criteria to be included in the examination are as follows: (1) 8 ≤ age ≤ 15; (2) satisfied the criteria of ADHD based on *Diagnostic and Statistical Manual of Mental Disorders 4th edition* (DSM- IV) and diagnosed with ADHD based on the *Korean version of Kiddie-Schedule for Affective Disorders and Schizophrenia-Present and Lifetime* (K-SADS-PL) in a semi-structured clinical interview conducted by a single board-certified psychiatrist; (3) intelligence quotient (IQ) score above 70; (4) have not received medication for ADHD treatment in the past or have received medication in the past but for less than 1 year and not within 4 weeks of the study. The exclusion criteria are as follows: participants with (a) congenital hereditary problems; (b) acquired brain injury such as cerebral palsy; (c) spasmodic disorder, other neurological disorders, or untreated dysesthesia (sensory disturbance); (d) diagnostic history or current state of schizophrenia and childhood psychosis; (e) intellectual disability; and (f) comorbid condition with obsessive-compulsive disorder, depressive disorder, or bipolar disorder. Comorbid conditions, such as anxiety or enuresis, will be allowed except for the symptoms in exclusion criteria. In addition, participants could apply the medication targeting other types of coexist pathologies, not with the symptoms which meet the exclusion criteria.

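### Interventions are compared on raw pre-post changes; ANCOVA would sharpen the first-period comparison at almost no cost, and baseline adjustment belongs beside the crossover change-score result, not in its place

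*Protocol article*

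**What the plan says.** Section 2.7 (Statistical analysis) of the protocol article fixes the response for the treatment comparison in both branches of its carry-over rule. Without significant carry-over, "we will compare the changes during specific interventions in both sequences". With it, "we will compare the changes in specific interventions during the first period". The section ends by saying that "comparisons between interventions will be performed using a two-tailed" t-test or a Mann-Whitney U test, chosen by normality. It names no covariate for this contrast; the repeated-measures ANOVAs there serve the rhythm types and the EEG tasks.

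The scores needed for adjustment are collected. Section 2.1 states: "Participants will be assigned randomly to either rhythm training followed by cognitive training or cognitive training followed by rhythm training". It adds that "Participants will have a 4-week washout phase between trainings" and that "pre- and post-training evaluations will be administered immediately before training and after the 4th week of training". Comparing changes in both periods requires a pre-training score in each.

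On size, section 2.3 says "Approximately 40 children with ADHD will be recruited". The article gives no standard deviation, pre-post correlation, target difference or power.

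**The concern.** A change score subtracts the whole pre-training score, that is, it fixes the baseline coefficient at 1. The coefficient that minimises the variance is usually smaller, so the subtraction puts part of the baseline's measurement noise into the result.

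- **First-period comparison.** This is an ordinary parallel-group comparison, and estimating the coefficient (ANCOVA) is the standard remedy. It also removes the error left by a chance difference between the groups at baseline.
- **Crossover comparison.** Each child already serves as his or her own control, so stable differences between children are gone before any baseline is used. Subtracting a pre-score in each period can then cost more noise than it removes.

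At stake is the precision of the efficacy contrast (the fourth hypothesis in the Introduction) in a trial with little to spare.

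**Working it through.** The plan has no figure of its own to reproduce. **From the document:** about 40 children, two sequences, two periods, pre- and post-scores around each training. **Assumed:** 20 children per sequence, SD 1 at every visit, the correlations shown, two-sided 5% level.

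**1. First-period comparison.** With pre-post correlation r, the variance per child is 2(1−r) for the change and 1−r² for ANCOVA. The ratio is (1+r)/2. Estimating the slope costs about 1/36 = 2.8% in variance at 40 children.

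| r | change | ANCOVA | ratio | ratio × 1.028 | 40 by change matched by |
|---|---|---|---|---|---|
| 0.5 | 1.00 | 0.75 | 0.75 | 0.77 | 30 |
| 0.7 | 0.60 | 0.51 | 0.85 | 0.87 | 34 |
| 0.9 | 0.20 | 0.19 | 0.95 | 0.98 | 38 |

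The last column is 40 × ratio, before the degree-of-freedom cost. The direction does not need equal variances: with SDs s₁ (pre) and s₂ (post), change variance minus ANCOVA variance is (s₁ − r·s₂)², which is never negative.

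**2. Chance imbalance, first period.** The SE of the baseline difference is √(2/20) = 0.32 SD, so a difference above 0.25 SD in either direction has a probability of about 43%. Given an imbalance d, the change-score estimate is off by (1−r)d in size; with r = 0.7 and d = 0.25 that is 0.3 × 0.25 = 0.075 SD. ANCOVA corrects this.

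**3. Crossover comparison, no carry-over.** Let Y be the difference between a child's two post-scores, X the difference between the two pre-scores, and ρ their correlation. The variance of Y adjusted for X, divided by the variance of Y − X, is (1+ρ)/2. With correlation w within a period and b between periods, ρ = (w−b)/(1−b).

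| structure | ρ | ratio | 40 by change matched by |
|---|---|---|---|
| all four scores equally correlated | 0 | 0.50 | 20 |
| first-order autoregressive, r = 0.5 to 0.9 (ρ = r/2) | 0.25 to 0.45 | 0.63 to 0.73 | 25 to 29 |
| w = 0.8, b = 0.5 | 0.60 | 0.80 | 32 |
| w = 0.9, b = 0.7 | 0.67 | 0.83 | 33 |
| w = 0.9, b = 0.5 | 0.80 | 0.90 | 36 |

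In the first row the best baseline coefficient is zero: the whole gain comes from not subtracting the baselines.

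Simulated power (3,000 trials, pre-post correlation 0.7, assumed true difference 0.4 SD) was 62% for change and 88% adjusted with equal correlations, and 61% and 78% with b = 0.55. Type I error stayed near 5%.

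**4. Crossover comparison, with carry-over.** Let δ be the true difference, c a carry-over from one training only, and β the fitted baseline slope.

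- *c present equally at the second pre- and post-score.* The change score cancels it and estimates δ. The adjusted analysis estimates δ − c(1−β)/2. With equal correlations β = 0, so for δ = 0.4 it gives 0.30 if c = 0.2 and 0.20 if c = 0.4.
- *c present at the second pre-score but gone by the second post-score.* The change score estimates δ + c/2, which is 0.60 for δ = c = 0.4. The adjusted analysis estimates δ + βc/2, which is 0.40 at β = 0.

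For r = 0.7 and equal correlations, the variances of the two estimates are ¼ × 1.20 × (2/20) = 0.030 (change) and ¼ × 0.60 × (2/20) = 0.015 (adjusted). With c = 0.4 persisting, the adjusted mean squared error is 0.015 + 0.20² = 0.055, against 0.030. In simulation, power for adjusted against change was 66% against 62% at c = 0.2, and 33% against 62% at c = 0.4.

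**The case against.** The strongest defence is that nothing in section 2.7 is wrong. Change scores are unbiased under randomisation, they are conventional, and an unseen analysis plan may add covariates. The first two points stand, and they make this a matter of efficiency, not validity. The third has less force: the article does not leave the contrast open, but names the change as the response and two tests that take no covariate.

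The second objection is that adjustment is not free in the crossover. This stands. The second pre-score is measured after the first training, and these are skill trainings for which the article itself treats carry-over as a concern. Step 4 shows that neither method dominates: persisting carry-over biases the adjusted estimate, and carry-over that fades during the second period biases the change score. The plan's carry-over test does not settle the matter. A non-significant result with about 20 children per sequence is weak evidence of absence. If the test is run on the sum of a child's two changes, a carry-over equal at the second pre- and post-score cancels and cannot be seen: the sum is δ + (c − c) = δ in one sequence and 0 + δ = δ in the other.

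Third, chance imbalance in stable traits between the sequences cancels in the crossover comparison. This also stands, so the imbalance argument bears mainly on the first-period comparison.

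**Conclusion.** The plan gives up precision by a stated choice.

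- **First-period comparison.** The case for ANCOVA is clear. Its pre-score precedes all training, so carry-over cannot touch it. Assuming equal variances, the variance falls by 25%, 15% or 5% at r = 0.5, 0.7 or 0.9, less about 3%. At r = 0.9 the net gain is only about 2%. Under the plan's rule this comparison applies to endpoints with significant carry-over.
- **Crossover comparison.** Without carry-over, adjustment lowers the variance by about 10% to 50%, before the same small cost. It is a bias-variance trade-off.

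A reader might infer that the change-score analysis is invalid, that adjusting is a free gain throughout, or that the 40 children are worth only 20 to 28. The documents support none of these. Randomisation keeps the change-score comparison unbiased apart from carry-over. The 20-to-28 range follows only from particular correlation structures; since the article gives no correlations, about 20 to 36 is the fairer statement. The adjusted crossover estimate should not simply replace the planned one.

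**What to change.** 1. **First-period comparison:** make it an ANCOVA of the first post-training score on intervention, with the first pre-training score as covariate. If the residuals are non-normal, run it on ranks or on transformed scores, so that the Mann-Whitney branch has a counterpart.
2. **Crossover comparison:** keep the change-score analysis. Pre-specify, as a supporting analysis, the difference between the two post-scores regressed on sequence with the difference between the two pre-scores as covariate. Report both estimates with confidence intervals for every crossover endpoint.
3. **Interpretation:** state in advance that a marked difference between the two crossover estimates may signal carry-over, and that the more favourable one will not be chosen.

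The cost is wording in the analysis section, one residual degree of freedom per adjusted model and one more reported estimate per endpoint. No new visits, measurements or children are needed.

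### A carry-over pre-test picks the analysis endpoint by endpoint, so the intervention comparison does not keep its nominal error rate, and the test has little power for small to moderate carry-over

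*Protocol article*

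**What the plan says.** The design is a two-sequence, two-period crossover (section 2.1): "Participants will be assigned randomly to either rhythm training followed by cognitive training or cognitive training followed by rhythm training". The ratio is not given. Section 2.3 gives the size: "Approximately 40 children with ADHD will be recruited". On the gap between periods, section 2.1 says: "Participants will have a 4-week washout phase between trainings to minimize a possible carryover effect".

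Section 2.7 opens the crossover analysis with the aim of the first step: "The study will undertake a comparative analysis of two intervention sequences and investigate the existence of carry-over effects". The tool is a t-test "on the change of each sequence for all crossover endpoints". The outcome decides what follows. If the test is not significant: "For variables that do not show significant carry-over effects, we will compare the changes during specific interventions in both sequences". If it is: "For variables that show significant carry-over effects, we will compare the changes in specific interventions during the first period". The section ends by planning a two-tailed t-test or a Mann–Whitney test between interventions, depending on normality. It gives no significance level for either step and does not define the carry-over statistic algebraically.

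**The concern.** This is the two-stage crossover procedure, in which a preliminary test chooses between a two-period and a first-period analysis. It is written into the protocol as a rule, so it is not a detail left to a later document.

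The second-stage test is not independent of the first. The carry-over contrast contains the period-1 changes, and the fallback test is computed from those same changes. An endpoint on which the sequences happen to differ in period 1 is therefore more likely both to switch and to be declared significant after switching.

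The comparison between the two trainings is hypothesis 4 in the Introduction. It is run on many scales (four questionnaires and five cognitive tools), so some endpoints will switch by chance alone. Those are the ones whose p-values can be trusted least. They would also rest on a different and less precise estimator than the rest, chosen by the data.

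**Working it through.** **Inputs.** From the document: about 40 children, two sequences, the switching rule, a two-tailed treatment test. Assumed, because the document is silent:
- 1:1 allocation, so 20 per sequence (16 was also tried for the false-positive rates);
- treatment test at 5%, carry-over test at 5% or 10%;
- normal changes with SD 1 in each period, and within-child correlation ρ of the two changes from 0 to 0.7;
- the carry-over statistic is the sum of the two period changes, compared between sequences.

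The plan states no power or error figure, so there is none to reproduce.

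**Step 1: why the two tests are linked.** Let d1 and d2 be a child's changes in periods 1 and 2. The carry-over test uses S = d1 + d2, the crossover test D = d1 − d2, and the fallback d1 alone.
- corr(S, D) = 0, so choosing the crossover branch does not distort the crossover test.
- corr(S, d1) = (1 + ρ)/√(2(1 + ρ)) = √((1 + ρ)/2), which is 0.71, 0.87 and 0.92 for ρ = 0, 0.5 and 0.7. The fallback is strongly tied to the event that triggers it.

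**Step 2: false positives with no treatment effect and no carry-over** (simulation of the written rule, 40,000 to 60,000 runs per setting, 20 per sequence):

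| ρ | Overall, 5% pre-test | First-period test after a switch, 5% pre-test | Overall, 10% pre-test | First-period test after a switch, 10% pre-test |
|---|---|---|---|---|
| 0 | 6.4% | 32% | 7.0% | 25% |
| 0.5 | 7.4% | 52% | 8.2% | 37% |
| 0.7 | 7.9% | 63% | 8.8% | 43% |

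The overall figure can be checked by hand as P(switch) × conditional rate + P(no switch) × 5%:
- ρ = 0: 0.05 × 0.32 + 0.95 × 0.05 = 0.016 + 0.0475 = 6.35%
- ρ = 0.5: 0.05 × 0.52 + 0.0475 = 7.35%
- ρ = 0.7: 0.05 × 0.63 + 0.0475 = 7.9%

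At ρ = −0.3 the overall rate is still 6.0%. With 16 per sequence the rates are almost the same. A single fixed crossover test on the same data gives about 5.0% for every ρ. A fresh simulation agreed with these figures within simulation error.

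**Step 3: power of the carry-over test.** The standard error of the between-sequence difference in S is √(2 × 2(1 + ρ)/20), which is 0.447 at ρ = 0 and 0.583 at ρ = 0.7. For a carry-over difference of 0.5 SD the noncentrality is 0.5/0.447 = 1.12 and 0.5/0.583 = 0.86. From the noncentral t with 38 degrees of freedom (5% test):

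| Carry-over (SD of change) | Power, ρ = 0.7 to ρ = 0 |
|---|---|
| 0.25 | 7–9% |
| 0.5 | 13–19% |
| 0.8 | 27–41% |
| 1.0 | 39–59% |
| 1.5 | 71–91% |

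**Step 4: what the rule protects when carry-over is real and treatment has no effect** (5% pre-test, false positives from ρ = 0 to 0.7):
- 0.5 SD carry-over: 18% to 47% under the rule, 19% to 51% if the crossover test is always used.
- 1.0 SD carry-over: 27% to 62% under the rule, 59% to 98% if the crossover test is always used.

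**Step 5: what a switch costs.** For a true treatment difference of 0.5 SD without carry-over, the crossover test has 58% power at ρ = 0 and 87% at ρ = 0.5. The first-period test has 33% to 34%.

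**The case against.** The strongest defence is that training effects may well outlast a 4-week washout. A rule that retreats to period 1 when carry-over appears then looks prudent, and dropping it leaves the crossover estimate exposed. This partly stands. At 1.0 SD of carry-over the rule lowers false positives materially, although it still leaves 27% to 62%. At 0.5 SD it is only marginally better than always using the crossover test. The fix must therefore admit that it does not cure carry-over bias.

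It is also fair that the overall inflation is moderate, about 1.4 to 2.9 points with a 5% pre-test. Most false positives still come from endpoints that do not switch.

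A reader might infer more than the document supports:
- *That a stated 5% level is broken.* No level is stated; 5% is my assumption.
- *That the trial cannot detect carry-over.* It has little power for small to moderate carry-over, but about 1.5 SD would usually be found.
- *That most switched endpoints are already significant by chance.* At ρ = 0 about two thirds are not. Only at ρ of about 0.5 and above do they become the majority.
- *That testing carry-over on change scores is itself a mistake.* The treatment comparison is also on changes. A residual effect that stays constant through period 2 cancels from the period-2 change, so under additivity it does not bias that comparison. The test matches the analysis that it guards.
- *That the two branches target different quantities.* Without carry-over they estimate the same treatment difference, with different precision.

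**Conclusion.** The point holds in this form: the switching rule in section 2.7 costs type I error when carry-over is absent and gives little protection when carry-over is small to moderate. The serious part is conditional. An endpoint that reaches the first-period test through the pre-test carries a false-positive risk of about 32% to 63% (25% to 43% with a 10% pre-test). Overall error is about 6.4% to 7.9%, or 7.0% to 8.8% with the 10% pre-test.

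The sizes rest on the assumed levels, equal allocation, normal changes with equal SD, ρ between 0 and 0.7, and reading the carry-over statistic as the sum of changes. The direction does not depend on the exact values: inflation appeared in every setting tried. Multiplicity over the many scales is a separate matter and is not in these figures.

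**What to change.** In section 2.7, delete the carry-over pre-test and the switching rule. Replace them with the following.

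1. One pre-specified analysis for every crossover endpoint: an unpaired comparison between sequences of each child's period-1 minus period-2 change, by t-test or, if non-normal, Mann–Whitney. The equivalent mixed model with treatment, period and sequence terms would also serve. This states what the between-intervention test at the end of the section is applied to.
2. For every endpoint, whatever its significance, report as supportive:
   - (a) the between-sequence difference in second minus first pre-training score with 95% CI, as a description of washout;
   - (b) the first-period-only estimate with 95% CI.
3. A sentence saying that the crossover estimate relies on the 4-week washout being adequate, and that omitting the pre-test does not remove bias from real carry-over.

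The cost is a rewording and two more columns per endpoint. The pre-training evaluations are already planned, so no new visits or participants are needed. The downside is that no data-driven fallback remains if carry-over is real. Readers would judge that from (a) and (b), and (b) is much less precise.

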In the present study, we will develop a rhythm-based assessment and training (RAT) that was designed to reflect the complexity of real-world rhythm processing. Four types of rhythmic sequences were generated based on a series of investigations that employed different levels of complexity in rhythmic stimuli (Essens and Povel, 1985; Grahn and Brett, 2007; Chen et al., 2008; Bengtsson et al., 2009). The types of rhythmic sequences are isochronous (ISO), syncopated (SYN), metric (M), and non-metric (NM) and thus, can serve as an assessment and training tool with an infinite array of test items tailored to individual abilities. Also, we will comprehensively investigate the timing ability in ADHD as measured by music indicators of the RAT and explore its relationship with ADHD symptoms and cognitive abilities as measured by diagnostic questionnaires and cognitive evaluation measurements. Electroencephalography (EEG) will be recorded to scrutinize each phase of information processing, including perception, maintenance and manipulation, and reproduction. Our hypotheses include: (1) RAT performance would significantly differ by the level of rhythmic complexity, (2) music indicators would be significantly correlated with ADHD diagnostic questionnaires and cognitive evaluation measurements, (3) band frequency activities of EEG would significantly differ by the phase of information processing, and (4) behavioral outcome measures would significantly differ by intervention types (i.e., rhythm-based training, cognitive training).

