The training session will consist of practice and main session. In the practice session, the participants will undergo eight practice trials, two trials for each of the four rhythmic sequences to be familiarized with the stimuli and task. In the main training session, participants will be asked to listen to, mentally rehearse the sequences, and tap the rhythmic sequences. A total of 60 trials of rhythmic sequences will be presented; however, the number of rhythmic sequences given to each of the four types of rhythmic sequence will vary upon the individual baseline ability. In the training session, a trial will consist of (1) rhythm presentation, (2) cue, (3) rhythm maintenance, (4) cue, and (5) rhythm reproduction. Table 1 presents overall structure of the RAT, tasks trials assigned across rhythmic sequence and session types (Please note that the number of trials assigned to each of the four rhythmic sequences in training provided is an example; the actual number of training trials will be determined based on the results of the assessment). The rhythmic sequences used in the assessment and training sessions will not overlap with each other. The RAT performance will be evaluated using the numbers of taps, the timing of taps, and the intervals between taps (i.e., tap onset to onset interval, TOA) as compared with those of the original rhythmic sequences. Presentation of RAT and recording of participants’ behavioral responses will be performed using E-prime software (Psychology Software Tools, Pittsburgh, PA, Version 3.0). At the end of each session, participants will be given a one-page performance evaluation report. A total time to completion will be approximately 30 min for both assessment and training.

**TABLE 1 T1:** Overview of RAT structure and task-trial assignment.

Session type	Task type	Number of trials in rhythmic sequence type			
		ISO	*M*	SYN	NM
Pre- Assessment	Maintenance/Reproduction	10/10	10/10	10/10	10/10
Training week 1	Maintenance-Reproduction	24	24	6	6
Training week 2	Maintenance-Reproduction	18	24	12	6
Training week 3	Maintenance-Reproduction	12	18	18	12
Training week 4	Maintenance-Reproduction	6	12	24	18
Post- Assessment	Maintenance/Reproduction	10/10	10/10	10/10	10/10

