##### 2.5.2.2. Stroop color and word test children’s version

Stroop color and word test (SCWT) is a neuropsychological assessment tool for evaluating the efficiency of the prefrontal lobe, especially attentional and executive functioning (Golden and Golden, 2002). This tool is frequently used for evaluating cognitive inhibition in children (Archibald and Kerns, 1999). The SCWT is composed of three subtest conditions of word, color, and color-word. In the first subtest, word condition, participants should read and speak the colored words printed in black ink. In the color subtest, participants were asked to read the bar of X’s, colored in red, blue, or green ink. Last, in the color-word subtest, colored words are printed a color incongruent with the printed name. Participants should ignore the letter and read the printed ink sequentially as in other subtests. For each subtest, participants should read the stimulus as quickly and accurately as possible within 45 s, and the raw scores will be scored according to the number of correct answers. Interference score is calculated as the difference between the color score and the color-word score. In the current study, the Korean version of SCWT was conducted through the E-Prime software (Psychology Software Tools, Pittsburgh, PA, Version 3.0).

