##### 2.5.2.3. Children’s color trails test

The children’s color trails test (CCTT) is a neuropsychological test that can evaluate frontal lobe function of child psychiatric disorders, including attention and executive function (Koo and Shin, 2008). Based on the adult version of the trail making test (TMT), the child’s version minimizes the disadvantages caused by age by avoiding dependence on letters and minimizes the influence of culture and language using colors and numbers instead of letters (Williams et al., 1995). The Korean version of standardized CCTT (Koo and Shin, 2008) was conducted during the study. The test consisted of two subtests: CCTT-1, which measures sequential processing power and psychomotor speed, and CCTT-2, which examines continuous divisional attention and cognitive flexibility (Reum et al., 2021). Under the researcher’s instruction, participants performed each subtest in consecutive order, performing a practice task prior to the actual task. In the first subtest, CCTT-1, participants should connect the numbers 1–15 as quickly and correctly as possible, without lifting the pencil from the paper. For the next subtest, CCTT-2, identical numbers are embedded in separate pink and yellow circles. Participants should connect the numbers sequentially from 1 to 15, alternating between colored circles. The raw score is calculated as the time for completing each task, and the number of errors committed was counted for ascending numbers or altered colors.

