##### 2.5.2.5. Comprehensive attention test

The comprehensive attention test (CAT), a Korean version of a computerized continuous performance task will be administered (Yoo et al., 2009). For each selective task, participants will be instructed to make the response to target stimuli and inhibit the response to non-target stimuli. Participants’ performance will be assessed by four main variables: (1) omission errors to measure inattention, (2) commission errors to measure impulsivity, (3) response time to measure the processing speed, and (4) response time standard deviation to measure the variability of the response time. All raw scores will be standardized into attention quotients (AQs), adjusted for age and gender by comparison with a normal population, and the average AQ is 100 with standard deviation of 15. In addition, two variables will be also collected: (1) d’ variable to measure whether participants discriminate target stimuli with non-target stimuli well, and (2) Beta (β) to measure the participants’ response bias whether there are more omissions or commissions in the event of error responses. The visual and auditory selective tasks each lasting 11 min.

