## 3. Discussion

The current study aims to develop RAT as a tool for assessing and training the time-related abilities of children with ADHD using a wide range of auditory stimuli organized in various types of rhythmic sequences. Additionally, the study will validate rhythm-based attention training for children with ADHD and its correlations with the behavioral diagnostic questionnaire and scores of cognitive evaluation tools for ADHD. In addition, they study will examine the efficacy of the training in comparison with general cognitive training. The use of EEG will aid in uncovering the nature of auditory rhythm processing in ADHD and in revealing the therapeutic mechanism of auditory rhythm at various levels of complexity. The present findings will contribute to the potential of rhythm-based training as a supplementary or alternative method for behavioral symptoms and cognitive functions of ADHD. The multifaceted data collected will provide valuable insights into the development of a computerized rhythm-based cognitive training program for ADHD and will enable tailored training agendas based on individual developmental stages and prognoses.

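### Unadjusted Pearson correlations across ages 8 to 15 let age alone produce a significant link between RAT and the cognitive tests scored without an age norm (Stroop, colour trails)

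*Protocol article*

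**What the plan says.** Section 2.7 (Statistical analysis) states that Pearson's "correlation test will be used to calculate the correlations between RAT performance and behavioral outcome measures". It names no covariate and no partial correlation. These correlations serve Hypothesis 2 in the Introduction, that "music indicators would be significantly correlated with ADHD diagnostic questionnaires and cognitive evaluation measurements". The Discussion also counts them as part of the validation of the rhythm training, through "its correlations with the behavioral diagnostic questionnaire and scores of cognitive evaluation tools for ADHD". Section 2.3 sets the age range at 8 to 15 and the size: "Approximately 40 children with ADHD will be recruited".

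The measures are on different kinds of scale:

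- **RAT** (Section 2.4.1): "The RAT performance will be evaluated using the numbers of taps, the timing of taps, and the intervals between taps", compared with the original sequence. No age norm is mentioned.
- **SCWT** (Section 2.5.2.2): "the raw scores will be scored according to the number of correct answers", plus an interference score that is the difference of two such counts. No age norm is mentioned.
- **CCTT** (Section 2.5.2.3): "The raw score is calculated as the time for completing each task", plus error counts. No age norm is mentioned.
- **Digit span and letter-number sequencing** (Section 2.5.2.1): raw or age-scaled is not stated.
- **ATA** (Section 2.5.2.4): the four main variables become T scores based on age and gender. The status of d' and beta is unclear.
- **CAT** (Section 2.5.2.5): attention quotients "adjusted for age and gender by comparison with a normal population". The status of d' and beta is again unclear.
- **K-CBCL** (Section 2.5.1.1): raw subscale sums converted to T scores.

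**The concern.** By norming ATA and CAT for age and gender, the protocol treats raw performance on those tests as depending on age. It does not carry this through to RAT, SCWT or CCTT. If older children both tap more accurately and finish the Stroop and trails tasks faster, two such scores will correlate across an 8-to-15 sample even when they are unrelated among children of the same age. A significant result would then be read as evidence that RAT reflects cognitive ability when it reflects maturation.

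The opposite problem arises with the normed scores. There the age-related part of RAT has nothing to correlate with and acts as noise, so a real association at a given age is diluted. The two groups of correlations therefore do not answer the same question, although the plan treats them alike.

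**Working it through.** The article gives no power, alpha or sample-size calculation for the correlations, so there is no stated figure to reproduce.

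**Inputs from the article:** n = 40 (Section 2.3), ages 8 to 15 (Section 2.3), plain Pearson test (Section 2.7).

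**Assumptions:** two-sided alpha of 0.05; age spread evenly over the range; correlation of age with RAT (a) and with the cognitive score (b) between 0.2 and 0.7 in absolute value; no association between the two scores at a fixed age.

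**Step 1, critical value.** With 38 degrees of freedom t = 2.024, so critical |r| = t / √(38 + t²) = 2.024 / √42.10 = 0.312.

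**Step 2, induced correlation.** If age is the only link, the expected correlation is r = a × b. For a = b = 0.5 this is 0.25.

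**Step 3, chance of a significant result.** By Fisher's z the standard error is 1/√37. For r = 0.25, atanh(0.25) × √37 = 0.2554 × 6.083 = 1.554, and P(Z > 1.96 − 1.554) = 34.2%. A simulation with 40,000 replicates per case gives 34.4%. It also gives the rate for the age-partial correlation (37 degrees of freedom).

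| a (RAT) | b (cognitive) | induced r | plain Pearson, simulated | plain Pearson, Fisher z | age-partial, simulated |
|---|---|---|---|---|---|
| 0.2 | 0.2 | 0.04 | 5.5% | 5.7% | 5.0% |
| 0.3 | 0.3 | 0.09 | 8.4% | 8.5% | 5.0% |
| 0.4 | 0.4 | 0.16 | 16.2% | 16.6% | 5.0% |
| 0.5 | 0.5 | 0.25 | 34.4% | 34.2% | 4.8% |
| 0.6 | 0.6 | 0.36 | 65.0% | 63.0% | 5.0% |
| 0.7 | 0.7 | 0.49 | 92.7% | 90.3% | 4.9% |
| 0.3 | 0.6 | 0.18 | 19.8% | 19.8% | 5.0% |
| 0.5 | 0.7 | 0.35 | 62.5% | 60.4% | 5.1% |

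**Step 4, normed comparators.** With the cognitive score made independent of age (an ideal norm), plain Pearson rejects in 4.7% to 5.2% of replicates. Age creates no false positives there.

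**Step 5, power against normed comparators.** If the association at fixed age is ρ and the comparator is free of age, plain Pearson estimates ρ × √(1 − a²). Taking a = 0.6 and ρ = 0.40 as an illustration, this is 0.40 × 0.8 = 0.32. By Fisher's z, power is P(Z > 1.96 − atanh(0.40) × √37) = P(Z > −0.62), about 73%, without dilution. It is P(Z > 1.96 − atanh(0.32) × √37) = P(Z > −0.06), about 52%, with it.

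**The case against.** **The size is not known.** No section gives a correlation of age with any RAT indicator. RAT yields several indicators over four sequence types, so one value cannot describe them all. At 0.3 or below for both scores the inflation is slight. This stands, and it is why the full range is shown.

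**The analysed score may not be the raw one.** Sections 2.5.2.2 and 2.5.2.3 say how the tests are scored, not which score enters the correlation. The CCTT is a standardised Korean version, and the Stroop interference score may depend on age differently from a count. This stands in part. The only scores described are unnormed, and the remark that CCTT reduces age disadvantage concerns dropping letters, not how completion time is scored. RAT itself has no norm in any case.

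**The correlations may be of changes.** Section 2.7 gives no time point, and the Discussion speaks of relating changes in musical responses to changes in symptoms. Change scores would be less exposed to age. This stands: the point concerns correlations of score levels, and it gives no ground for confining every pair to the first pre-training evaluation.

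**A full analysis plan may adjust for age.** It may, but the analysis stated here is bivariate.

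Three stronger readings are tempting but unsupported:

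- A reader might infer that age can produce the link between RAT and cognition in general. It cannot where the norms remove age, as intended for the main ATA variables and CAT.
- A reader might infer that the results would be misread as specific to executive function. No section plans that inference, and the normed ATA also measures inhibitory control.
- A reader might infer confounding by sex. Nothing here demonstrates it.

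**Conclusion.** The point holds for RAT against SCWT and CCTT. It extends to digit span, letter-number sequencing, d' and beta only if these are analysed unnormed. For such pairs, a significant plain Pearson correlation cannot separate a link with cognition from shared dependence on age. The false-positive rate runs from close to nominal (5.5% at age correlations of 0.2) to 93% (at 0.7). Where this trial lies in that range cannot be determined from the article. For age-normed comparators the risk is lost power, not false positives, provided the norms remove age in this sample. Hypothesis 2 also covers questionnaires and normed tests, so a few SCWT or CCTT correlations would not settle it alone. The affected part is nonetheless easily protected.

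**What to change.** In Section 2.7, replace plain Pearson with partial correlation adjusted for age (in months if available), or regression on age, for every correlation of score levels between RAT and an outcome measure. Use age-normed scores where the tool provides them, and state for SCWT, CCTT, digit span, letter-number sequencing, d' and beta which score is analysed. State the time point. Any correlation of change scores can stay as a separate, labelled analysis. Sex may be added as an optional covariate.

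The cost is one degree of freedom for age (38 to 37 at n = 40), and one more if sex is added. No new data are needed: age is an eligibility criterion, and age and gender are already required for the ATA and CAT norms.
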